## **6- Origin, nature and mode of circulation of the personal data collected**

7

The medical data collected for each patient included will be entered into the CRFs provided by the sponsor. A CRF, indicating the initial of the first and last name of the patient, as well as the serial number of entry into the study, is assigned to each patient. The investigating doctor is responsible for filling in all the required information.

The promoter's CRA will keep the calendar of inclusions up to date, will check with the investigators that the injections have indeed been carried out, and will collect the CRFs once the final visit has been carried out. At each monitoring visit, the sponsor's CRA will retrieve the original sheets of the CRFs already completed and bring them to the sponsor's premises where they will be archived, according to the order number of entry into the study.

At the end of the study, all the data recorded in the CRFs will be entered into an Excel® database. The input work will be carried out within the Labrha research unit. Before the database is frozen, any questions ("queries") will be sent, by the CRA monitor, to the investigators who will have to answer them on the sheets provided for this purpose, by sending them back to the sponsor in a T envelope delivered to investigators. In the event of data not being available, the mention ND will be assigned to the missing variable.

### **6-1. Data Privacy:**

The collection and processing of data by the investigator or the members of his team is carried out with respect for the anonymity of the patients, and the medical information obtained for each patient during this study is considered confidential; any disclosure to a third party is prohibited.

[figure not shown]

The promoter's CRAs and any person authorized by the promoter must have access to the source documents in order to verify the accuracy of the data entered in the observation book and the application of the regulatory requirements.

The promoter guarantees the respect of the confidentiality of the data of the participants in the study in accordance with the European directives and the French law "Informatique et Libertés".

[figure not shown]

Patients will be informed of this procedure and of their right to access and rectify data concerning them. During the presentation of the results of the study, the identity of the participating patients will remain confidential.

## **6-2. Use of information and publication**

All information concerning the study is confidential and remains the property of the promoter. The details will only be disclosed to persons involved in the approval or conduct of the study, these persons are bound by professional secrecy in the same way as the investigators, in accordance with article R. 5120 of the CSP.

The investigator can only use this information within the framework of this study and can only use the data concerning the patients if the sponsor gives the authorization. For this, the investigator must present, in detail, the conditions of use of the data, their archiving, and will be in this context, responsible for the database thus created.

At the end of the study, after validation by the coordinator, the study data will be submitted for presentation at scientific congresses (French Society of Rheumatology and one or more international congresses of rheumatology and/or stomatology) and submitted for publication in a peer-reviewed journal chosen jointly by the principal investigator, coordinator and sponsor. In the absence of agreement between the parties, it is up to the promoter to choose the journal to which the manuscript will be submitted.

[figure not shown]

### 6-3. Data Archiving

In order to guarantee the protection of patients and the validity of the data from a regulatory point of view, these will be kept for a period of 15 years. No document (paper or electronic) of the study should be destroyed without the prior written consent of the sponsor.

### 7- Duration of the study

This observational study requires a follow-up period of 6 months. The expected start date of recruitment is 01/04/2016. Recruitment will end when 44 patients have been included, in order to obtain 40 complete files, taking into account a percentage of trial dropouts and loss of follow-up of 10%. Recruitment time is estimated at 6 months. The total planned duration of the study is therefore 12 months.

### 8- Data analysis method

#### 8-1. The analysis of this observational study will be purely descriptive.

The demographic, clinical and radiographic qualitative variables will be described by their number, percentage and missing data by response modality and the quantitative criteria by their number, average, standard deviation. In the case of quantitative criteria with asymmetrical behavior, they will be presented with their median and the interquartile range (25th percentile - 75th percentile).

#### 8-2. The endpoint is the response to treatment.

The aim of the study being the search **for predictive factors of response to treatment**, it is not relevant to determine a primary endpoint. We will study the possible correlation between the response to the treatment and the level of pain on D0, the duration of the symptoms, the presence of a limitation of the mouth opening, and the existence of radiological lesions of osteoarthritis on the panoramic dental picture.

[figure not shown]

The response to the treatment will therefore be estimated by 3 complementary methods and for each of them the predictive factors of response (YES/NO) will be studied. Each patient will be classified into a treatment response category: YES or NO depending on:

1. The patient's assessment of the effectiveness (effective and very effective = YES, not or only slightly effective = NO),
2. Reduction in pain of at least 3 points or at least 50% on the Likert scale.
3. The degree of patient satisfaction (Very satisfied and fairly satisfied = YES, little or not satisfied = NO),

We will look for predictive factors of response or non-response, first in univariate analysis then in multivariate analysis by integrating all the factors with a  $P < 0.1$  in the univariate analysis, as well as possible confounding factors such as age, gender, taking NSAIDs, wearing a tray.

The main analysis will be carried out on the per-protocol population including only patients for whom all the data at D0 and D180 are available, then confirmed by ITT. For patients who do not have D180 data, the latest data available (D90) will be used (LOCF). The regression coefficients of the multivariate models (ANCOVA and mixed model) will be considered significant if the degrees of significance are less than 5%. Statistical analyzes will be performed with XLStat software.

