## 1-Proof of research:

Osteoarthritis of the temporomandibular joint (TMJ) is a frequent cause of arthromyalgia of the face grouped under the acronym DAM (Dysfunction of the Manducator Apparatus). It can be expressed by a wide range of symptoms dominated by pain in the TMJs, associated or not with limitations in mouth opening, or even by blockages, joint noises and other signs such as bruxism, otalgia or tinnitus. These pains can be accompanied by functional disorders such as a limitation of the mouth opening, evaluated by the inter-incisor distance (IDI), sometimes linked to a dislocation of the disc (or meniscus) which is interposed between the condylar process of the mandible and the glenoid cavity of the temporal bone. The management of this pain is essentially based on empirical means, prescribed out of habit and without any real evaluation (analgesics, NSAIDs, muscle relaxants) as well as on the wearing of occlusal splints and/or occlusal equilibration by adding composite resins. In the event of failure of first-line treatments, the treatment is based on corticosteroid infiltrations, the effectiveness of which is transient, or on the injection of hyaluronic acid (HA) also called viscosupplementation.

1

A meta-analysis including 19 studies showed that in DAM in general (12 with disc problems and 7 with inflammatory flare-ups of degenerative arthropathy) (1) HA injections provide a greater reduction in pain than placebo (saline solution) in all cases where it was compared to it, and overall comparable to corticosteroid infiltrations. In another meta-analysis that included 18 studies on the use of HA in TMJ osteoarthritis, Escoda-Francolí et al (2) reached similar conclusions and proposed a "Strong" strength of recommendation regarding the indication of viscosupplementation in degenerative TMJ disorders (osteoarthritis and meniscopathy). Finally, the authors of the Cochrane review (3) conclude that HA injections provide a long-term improvement in the symptoms of TMJ osteoarthritis, that their beneficial effects are equivalent to those of glucocorticoids, and that one can optimize their results by combining them with arthrocentesis.

[figure not shown]

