The objective of this research is therefore not to demonstrate the effectiveness of viscosupplementation in painful degenerative pathologies of TMJ **but to seek clinical factors predicting the success or failure of treatment** such as clinical severity before the injection, the presence of a limitation of the mouth opening or the duration of the symptoms.

For this we place ourselves **in the conditions of daily practice, in patients with symptomatic temporomandibular osteoarthritis with no other selection criteria** than the opinion of the investigator concerning the merits of viscosupplementation and the agreement of the patient participating in the research. **It in no way modifies the patient's therapeutic management and imposes no other constraint on him than filling in simple questionnaires commonly used in daily practice, in the monitoring of this pathology.**

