#### 3-1. During the selection visit (D0), the following elements will be collected:

- Demographics (gender, age, height, weight)
- Length of pain
- The target side

[figure not shown]

- Previous treatments for the pathology evaluated (NSAIDs, analgesics, muscle relaxants, infiltration of corticosteroids into the painful TMJ, injections of hyaluronic acid into the painful TMJ, specific rehabilitation of the oral sphere, wearing an occlusal splint)
- The search for bruxism, noises and / or crackles during chewing,
- TMJ pain on chewing measured on an 11-point numerical scale, "0" meaning "no pain" and "10" meaning "intolerable pain" (Likert 0-10),
- TMJ pain on palpation (Likert 0-10),
- The inter-incisor distance (IID) at the maximum opening of the mouth, measured in millimeters using a caliper.

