**3-2. During the visits at 3 (D90) and 6 months after the injection (D180) the following elements will be collected:**

- TMJ pain when chewing (Likert 0-10),
- TMJ pain on palpation (Likert 0-10),
- IID at maximum mouth opening (mm)
- Patient satisfaction with the treatment (4-point Likert where 0 means "Not satisfied" and 3 means "Very satisfied")
- The patient's perception of the effectiveness of the treatment (4-point Likert where 0 means "Not effective" and 3 means "Very effective")
- The patient's perception of the reduction in pain in 6 categories: [0%]; [1-24%], [25-49%], [50-74%], [75%-99%], [100%]
- The change in his consumption of analgesics or anti-inflammatories compared to D0 ([YES/NO] and if [YES] quantification on a 5-point Likert scale ([1-24%], [25-49%], [50-74%], [75%-99%], [100%]))
- Any adverse effects during the D90 visit (to ensure quality monitoring of the treatment)

[figure not shown]

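### Section 8-2 names mouth opening as a yes/no predictor although it is measured in millimetres; naming baseline inter-incisor distance in mm would be a cheap improvement.

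*Protocol*

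**What the plan says.** The study's aim is to find clinical factors that predict success or failure of the injection. Section 1 of the Protocol gives examples, among them "the presence of a limitation of the mouth opening or the duration of the symptoms". Section 8-2 repeats the mouth-opening item as "the presence of a limitation of the mouth opening", beside "the level of pain on D0, the duration of the symptoms" and radiological lesions.

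Section 1 also says that limitation is judged by the inter-incisor distance. Section 3-1 lists this baseline item: "The inter-incisor distance (IID) at the maximum opening of the mouth, measured in millimeters using a caliper". Section 3-2 collects the same distance in mm at D90 and D180. Section 3-1 has no separate yes/no item for limitation, and no section gives a threshold in mm.

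On the analysis, section 8-2 states: "The response to the treatment will therefore be estimated by 3 complementary methods". Predictors are sought for each method, first one at a time, "then in multivariate analysis by integrating all the factors with a" univariate P below 0.1. Multivariate coefficients are judged at 5%. Section 7 plans 44 inclusions for 40 complete files. Section 8-3 calls the study purely exploratory and sets no power.

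**The concern.** As worded, the predictor is an attribute that is present or absent. Since only the distance in mm is collected, that attribute has to be derived from the distance after data collection. Two things follow.

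First, turning a measured quantity into two groups usually throws information away, and with about 40 patients there is little to spare. Pain and duration are not treated this way in the same sentence.

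Second, if the threshold is still open when responses are known, it can settle where the groups differ most. A chance association then passes the P < 0.1 screen, or looks significant, more often than the nominal level suggests.

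**Working it through.** **Sample size.** The one design figure that can be reproduced is the 44 in section 7: 40 × 1.10 = 44. (Dividing instead, 40/0.90 = 44.4, gives 45; the difference is immaterial here.) The checks below use n = 40. The Protocol states no standard deviation for the distance, response rate, effect size or share of limited patients, so these are assumptions, shown over a range where possible.

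**Information lost by dichotomising.** For a normally distributed predictor with a linear effect, the efficiency of a two-group version relative to the continuous one is φ(z_p)² / [p(1 − p)]. Here p is the share classed as limited, z_p the matching normal quantile and φ the normal density.

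| p | Calculation | Efficiency | Lost | Effective n of 40 |
|---|---|---|---|---|
| 0.50 | 0.3989² / 0.25 | 0.637 | 36% | 25.5 |
| 0.30 | 0.3477² / 0.21 | 0.576 | 42% | 23.0 |
| 0.20 | 0.2800² / 0.16 | 0.490 | 51% | 19.6 |
| 0.10 | (same formula) | 0.342 | 66% | 13.7 |

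The formula is symmetric, so a range of 20% to 50% limited also covers 50% to 80%. Outside 20% to 80% the loss is larger.

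**Power under a linear effect.** Simulation with n = 40, two-sided 5%, a normal predictor, a logistic model, about 50% responders, a score-type test and 10,000 runs:

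| Assumed OR per SD | In mm | 50% limited | 30% limited | 20% limited |
|---|---|---|---|---|
| 2.0 | 52% | 37% | 34% | 29% |
| 2.5 | 73% | 53% | 50% | 41% |
| 3.0 | 85% | 67% | 63% | 53% |

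With about 60% responders and a likelihood-ratio test, the row for OR 2.5 is 74%, 54%, 51% and 45%. The last column varies somewhat with the set-up; the ordering does not.

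**Power under a step effect.** The ranking reverses if response truly changes at a threshold and the cut is placed exactly there. With n = 40, about 60% responders and an assumed step OR of 6:

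| Share limited | Dichotomised | In mm (linear) |
|---|---|---|
| 50% | 76% | 58% |
| 30% | 71% | 49% |
| 20% | 59% | 34% |

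**False positives if the cut follows the data.** Simulation with no true effect, n = 40, response rates of 50% to 70%, 20,000 runs each, one response definition, univariate test:

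| How the predictor is formed | P < 0.05 | P < 0.1 |
|---|---|---|
| Continuous, no cut | 5.0–5.3% | 10.4–11.0% |
| Median cut fixed in advance | 4–5% | 8–10% |
| Best of three cuts (30/50/70%) | 12–13% | 22% |
| Best cut in the central 60% | 29–30% | 48–49% |

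The P < 0.1 column corresponds directly to the univariate entry screen in section 8-2. The Protocol's 5% rule applies to the multivariate coefficients, so the P < 0.05 column is only a univariate analogue of it.

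**The case against.** **The dichotomy is implied, not specified.** Section 8-2 gives a narrative list of topics rather than a model. It does not rule out analysing the distance in mm, and its search is not expressly confined to the four named items. This stands in part: a reader might infer that the plan certainly discards a third to a half of the information, and the text does not settle that. But both places that name the factor use the yes/no form, while its neighbours keep their scale. If mm was intended, the wording should say so.

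**A cut-off belongs in a statistical analysis plan.** This stands for the threshold. A plan not shown here may fix it, which would remove the data-driven risk. It would not remove the information loss, because the Protocol itself names the binary form.

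**The 30% error rate is a worst case.** This stands. A reader might infer that this is the error rate of the planned analysis. It requires a search over every cut in the central 60%, and the Protocol proposes no such search.

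**Dichotomising may be the better choice.** Section 1 presents limitation as a sign that some patients have and others do not. Under a step effect at the correct cut, the binary form wins, as shown above. So the change is not free of downside. Still, that advantage needs the right threshold to be known, and the Protocol names none.

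**Little is at stake.** Section 8-1 calls the analysis purely descriptive, section 8-3 calls the study exploratory, and no power target is missed. This lowers the severity. It does not remove the point, since finding predictors is the study's sole aim and section 8-2 still applies significance rules.

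**Conclusion.** The point holds as a cheap improvement of low to moderate severity. The Protocol names a yes/no form of a variable that it collects only in mm, and gives no threshold.

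The loss of about 36% to 51% of the information (40 patients counting as about 20 to 25) rests on three assumptions: a roughly normal distance, a roughly linear effect on the logit, and 20% to 50% of patients classed as limited. The documents establish none of these, and the loss can turn into a gain if the effect is a step at a known threshold.

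The inflated false-positive rate, about 12% for three cuts and up to about 30% for a wide search, is a secondary risk. It arises only if the cut-off is still open once responses are known.

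**What to change.** In section 8-2, replace the mouth-opening item with D0 inter-incisor distance in mm, entered as a continuous predictor in the univariate and multivariate models, with the odds ratio reported per 5 mm, for example. Align the wording of the objective in section 1. Report any yes/no limitation only as a secondary or descriptive variable, at a justified cut-off in mm fixed before the database is frozen.

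The cost is a change of wording: no new data, visits or patients. The price is the assumption of a roughly linear effect, with lower power if the truth is a step at a known threshold. Keeping the pre-fixed yes/no version as a secondary analysis covers part of that case.

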## **2- Population concerned:**

Forty patients with temporomandibular osteoarthritis confirmed radiologically by a pantogram dating less than 12 months and justifying, in the opinion of the rheumatologist and/or the dental surgeon, viscosupplementation.

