### **Inclusion criteria:**

Those in **daily clinical practice**, i.e. all ambulatory patients over 18 years of age, of both sexes, whose clinical diagnosis of temporomandibular osteoarthritis is confirmed by a dental panoramic radiograph less than 12 months old, and for which the indication for viscosupplementation has been selected by the medical specialist, rheumatologist or dental surgeon, on the basis of the usual clinical criteria (pain, discomfort when chewing, insufficient efficacy or poor tolerance of analgesics and/or anti-inflammatories).

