##### 4-1. During the initial visit, the investigating doctor :

- gives the patient the information note, answers their questions and obtains their oral consent,
- verifies that the inclusion and exclusion criteria are respected,
- completes, in the data collection notebook assigned to the patient, according to the methodology developed in § 3-1,
- fills in the section "treatments for temporomandibular osteoarthritis", all treatments being authorized according to the rules of an observational study, provided they are collected,
- checks that the dental panoramic X-ray is less than 12 months old and asks for another one if necessary, as recommended before any intra-articular injection into the ATM.
- schedules or performs the intra-articular injection of HAppymini® hyaluronic acid himself. The injection may be performed the same day or for organizational reasons within a maximum period of 15 days, in order to limit the risk of variation in the clinical condition between the assessment and the date of the injection.

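### The radiological predictor in section 8-2 is also an entry requirement, so if eligibility is respected it is constant and its association with response cannot be estimated.

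*Protocol*

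**What the plan says.** Protocol section 8-2 states that the study looks for factors that predict response. It lists four to be related to response. Three are clinical: "the level of pain on D0, the duration of the symptoms, the presence of a limitation of the mouth opening". The fourth is radiological and is worded as a matter of presence or absence: "and the existence of radiological lesions of osteoarthritis on the panoramic dental picture". Response is classified in three ways, and "for each of them the predictive factors of response (YES/NO) will be studied". The search proceeds "first in univariate analysis then in multivariate analysis by integrating all the factors with a" univariate P value below 0.1, together with possible confounders.

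Section 2 describes the sample as "Forty patients with temporomandibular osteoarthritis confirmed radiologically by a pantogram dating less than 12 months". Its inclusion criteria ask for patients "whose clinical diagnosis of temporomandibular osteoarthritis is confirmed by a dental panoramic radiograph less than 12 months old".

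Section 3-1 opens with "During the selection visit (D0), the following elements will be collected" and then lists demographics, pain duration, target side, previous treatments, bruxism and joint noises, two pain scores and the inter-incisor distance. No radiographic item is among them, and section 3-2 adds none at D90 or D180. In section 4-1 the investigator verifies the eligibility criteria and "checks that the dental panoramic X-ray is less than 12 months old and asks for another one if necessary". Section 8-1 nevertheless announces a description of radiographic variables, without naming any.

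**The concern.** A predictor can be related to an outcome only if it differs between patients. Here the same type of film serves twice: it must show osteoarthritis for the patient to enter, and then the presence of osteoarthritis on it is to be tested as a predictor. Under the entry rule nobody is in the NO category.

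What is at stake is one of the four planned predictor analyses, under each of the three response definitions. A later statistical analysis plan can define a model or a coding, but it cannot make a constant vary. If a graded reading is not collected at D0, it would have to be recovered afterwards from stored films, possibly by someone who already knows the outcome.

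**Working it through.** **Inputs.** Complete files planned: 40; patients to include: 44; allowance for loss: 10% (section 7). Predictor: existence of lesions, yes or no (section 8-2). Entry condition: confirmation on the film (section 2). Entry rule for the multivariate model: P < 0.1 (section 8-2). The protocol gives no response rate or effect size; section 8-3 says the sample size was not calculated.

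**The plan's own figure.** 40 × 1.10 = 44, as stated; 40 / (1 − 0.10) = 44.4, or 45 rounded up. The one-patient difference has no bearing here.

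**Step 1: the predictor under the entry rule.** Let x = 1 if lesions exist and 0 otherwise. With x = 1 for every patient, the mean is 1 and the variance is Σ(x − 1)² / N = 0, for N = 40 and for N = 44.

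**Step 2: what can be estimated.**
- Correlation: cov(x, y) / (SD(x) × SD(y)) = 0/0, undefined.
- Odds ratio: the lesion-free row of the 2 × 2 table is (0, 0), so the ratio is 0/0.
- Regression: the design matrix [intercept, x] has two identical columns, so its rank is 1 of 2 and x has no coefficient of its own.
- P value: with an empty row only one table is possible. A package that prints an exact P value would print 1, which carries no information.

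The P < 0.1 rule therefore cannot be met, whichever response definition is used.

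**Step 3: what if a few lesion-free patients entered against the criterion?** The protocol gives no number, so this is an assumption shown over a range. Take 40 patients, k of them lesion-free, an overall response rate of 50% to 70%, and the most extreme split: every lesion-free patient is a non-responder. For k = 2 at 60% (24 responders, 16 non-responders), the probability that both are non-responders is (16 × 15) / (40 × 39) = 240/1560 = 0.15. The other two tables are more probable, so the two-sided Fisher P is 0.15. The smallest attainable values are:

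| Lesion-free patients (k) | 50% respond | 60% respond | 70% respond |
|---|---|---|---|
| 1 | 1.00 | 0.40 | 0.30 |
| 2 | 0.49 | 0.15 | 0.08 |
| 3 | 0.23 | 0.06 | 0.02 |
| 4 | 0.11 | 0.02 | 0.005 |

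One such patient can never bring the factor below 0.1, and two can do so only at the top of the assumed range. Any less extreme split gives larger values. A few enrolments against the criterion would therefore not rescue the analysis in practice.

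**The case against.** Four points can be made for the plan.

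- *The study is exploratory.* Section 8-1 calls the analysis purely descriptive, section 8-3 calls the study purely exploratory, and section 8-2 names no primary endpoint. A constant factor drops out; it biases nothing and creates no false finding. This stands, and it limits the severity.

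- *Radiology is not central to the objective.* Section 1 gives clinical severity, limited mouth opening and symptom duration as examples of predictors, and radiology is not among them. A reader might infer that the study loses one of its main questions. The documents do not support that: the list in section 1 is open, but the radiological factor appears only in the analysis list of section 8-2.

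- *The factor might vary after all.* Section 1 speaks of no selection beyond the investigator's opinion and the patient's agreement. Film age is the only feature of the film that section 4-1 spells out for checking. The inclusion criterion does not say that lesions must be on the target side. But section 1 still refers to patients with symptomatic osteoarthritis, section 4-1 also has the investigator verify the inclusion criteria, and loose entry would breach section 2. Lesions at the target joint could differ between patients, but section 8-2 speaks of lesions on the film and does not name the joint. These readings strain the text, though they show that the wording needs reconciling.

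- *A severity reading may be collected.* From the D0 list a reader might infer that no radiographic grade exists anywhere. That goes too far. Section 8-1 presupposes radiographic variables, and the CRF is not among the documents. What can be said is that section 3-1 omits an item that sections 8-1 and 8-2 rely on.

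**Conclusion.** The point holds at moderate severity. As written, the entry rule in section 2 fixes the fourth predictor in section 8-2 at YES for 40 of 40 (or 44 of 44) patients, so its relation to response cannot be estimated and it can never enter the multivariate model. This rests on two assumptions: that eligibility is applied as stated, and that existence means presence or absence, as the text says. No grade, score or lesion list in the protocol suggests otherwise.

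The loss is confined to one of four exploratory predictors. The other three remain estimable and are not biased, and the sample size does not depend on this factor, so the study as a whole is not undermined.

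**What to change.** Choose one of two changes before enrolment.

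1. **Keep a radiological predictor.** In section 3-1 add one item: radiographic severity of the target temporomandibular joint, as an ordinal grade or a count of listed lesions, with the scale fixed in advance. The investigator reads it on the film already required for eligibility and records it before the injection, so the reading cannot be influenced by the outcome. In section 8-2 replace existence of lesions with this item, entered as a single ordinal term.
2. **Drop it.** Delete the factor from section 8-2, state three candidate predictors, and align the mention of radiographic variables in section 8-1.

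The first option needs no new imaging. Its cost is one CRF line, one sentence in section 8-2, and the work of choosing and defining a scale, since the protocol names none. The second costs a sentence in section 8-2 and the matching edit in section 8-1. Neither changes treatment, eligibility or sample size.

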### **8-3. Justification of the number of subjects**

The study being purely exploratory, the number of subjects required is not possible to determine a priori. A number of 40 patients was therefore chosen by the study's scientific committee, as likely to provide sufficient information to allow hypotheses to be put forward on the question posed while allowing reasonable feasibility.

[figure not shown]

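### Section 8-2 admits its pre-named factors to the adjusted model only after an unadjusted P<0.1 test, so a factor masked by a listed confounder can drop out with no adjusted estimate

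*Protocol*

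**What the plan says.** Section 1 of the protocol gives the purpose of the study: not to show efficacy "but to seek clinical factors predicting the success or failure of treatment". Section 8-2 names four candidate factors in advance: "the level of pain on D0, the duration of the symptoms, the presence of a limitation of the mouth opening, and the existence of radiological" changes on the panoramic film. Response is coded YES/NO in three ways ("The response to the treatment will therefore be estimated by 3 complementary methods").

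The selection rule follows in 8-2: "We will look for predictive factors of response or non-response, first in univariate analysis then in multivariate analysis by integrating all the factors" whose univariate P is below 0.1, "as well as possible confounding factors such as age, gender, taking NSAIDs, wearing a tray". The confounders enter whatever their P value; the candidate factors do not. Coefficients of the multivariate models "will be considered significant if the degrees of significance are less than 5" percent.

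Section 8-3 calls the study exploratory and says that 40 patients were chosen "as likely to provide sufficient information to allow hypotheses to be put forward on the question posed". Nothing in the protocol keeps a pre-named factor in the adjusted model if it fails the screen.

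**The concern.** By listing age, gender, NSAIDs and the tray as possible confounders, section 8-2 accepts that the crude link between a factor and response may be distorted. It then uses that crude link to decide which factors are adjusted. If a confounder pulls the crude association towards no effect, the factor fails at P<0.1 and the adjustment that would have uncovered it is never made.

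One example: NSAIDs lower the pain recorded at D0, and NSAID users respond less often. If higher D0 pain truly goes with poorer response, the two effects partly cancel in the crude comparison.

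The candidates are four factors named beforehand, not a long list that needs thinning. In a study meant to generate hypotheses, wrongly discarding a candidate is one of the main ways to fail. This point is about missed factors, not about multiplicity.

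**Working it through.** **The plan's own figure.** The only sample-size arithmetic is in section 7: "Recruitment will end when 44 patients have been included, in order to obtain 40 complete files", allowing 10% for dropout. 40 x 1.10 = 44, which reproduces. The calculations below use n = 40.

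**Inputs.** From the protocol: n = 40, screen at P<0.1 (taken as two-sided), final test at 5%, confounders age, gender, NSAIDs and tray. Assumed, because the protocol gives no figures: 60% YES, half the patients on NSAIDs, the size of the NSAID effects, and a true adjusted odds ratio (OR) for D0 pain. Firth logistic regression with Wald tests stands in for the multivariate model.

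**Step 1: why masking happens.** As an approximation, with the SD taken within NSAID groups, crude log OR = b + g x d. Here b is the true log OR of D0 pain, g the log OR of NSAID use, and d the slope of NSAID use on D0 pain. If NSAIDs lower pain by s SD and half the patients take them, d = -0.25s / (1 + 0.25s²).

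- Strong: OR 0.5, NSAID OR 1/3, s = 1. d = -0.25/1.25 = -0.20. Crude log OR = -0.693 + (-1.099)(-0.20) = -0.473, so the crude OR is 0.62 instead of 0.50.
- Moderate: OR 0.5, NSAID OR 0.5, s = 0.5. d = -0.125/1.0625 = -0.118. Crude log OR = -0.693 + (-0.693)(-0.118) = -0.612, crude OR 0.54.
- Other direction: OR 2, NSAID OR 1/3, s = 1. Crude log OR = 0.693 + 0.220 = 0.913, crude OR 2.49, further from 1.

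**Step 2: detection with and without the screen.** With the screen means unadjusted P<0.1 and then adjusted P<0.05; without it means adjusted P<0.05 directly.

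| Scenario (true OR per SD; NSAID OR; shift in D0 pain) | With screen | Without | Loss (points) |
|---|---|---|---|
| 0.5; 0.33; 1 SD | 25% | 31% | 6 |
| 0.4; 0.25; 1 SD | 41% | 51% | 10 |
| 0.4; 0.25; 1.5 SD | 42% | 52% | 10 |
| 0.5; 0.33; 0.5 SD | 27.8% | 31.5% | 3.7 |
| 0.5; 0.5; 0.5 SD | 30.9% | 32.5% | 1.6 |
| 0.5; 0.5; 0.25 SD | 31.2% | 32.3% | 1.1 |
| 0.5; 0.67; 0.5 SD | 31.5% | 32.3% | 0.8 |
| 2; no confounding | 32.1% | 32.4% | 0.3 |
| 2; 0.33; 1 SD (other direction) | 27.8% | 27.8% | 0 |

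The first three rows come from 1,500 simulated trials each; repeats with 2,000 to 4,000 agreed to within 3 points. The other rows used at least 2,000.

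**Step 3: sensitivity to the set-up.** A separate simulation used likelihood-ratio tests, a response near 50%, one binary confounder and true ORs of 2 to 3 per SD. Losses were 0 to 0.2 points when the confounder had no effect, 1 to 4 when it was uncorrelated with the factor, 6 to 16 with confounder OR 1/3 and latent correlation 0.5 to 0.7, and 15 to 27 with confounder OR 1/5 at the same correlations. The pattern is the same; the size follows the assumed masking.

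**Step 4: false positives.** With no true effect, removing the screen raises the per-test rate from about 1.4% to 2.5%, still below 5%.

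**Step 5: precision.** With an adjusted standard error of about 0.42, a true OR of 2 per SD gives exp(0.693 ± 1.96 x 0.42) = exp(-0.130) to exp(1.516), a 95% CI of about 0.9 to 4.6.

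**Step 6: room in the model.** At 60% YES the smaller response group has 0.4 x 40 = 16 patients. Four factors plus four confounders in one model leave 16/8 = 2 per coefficient; one factor plus four confounders leaves 16/5 = 3.2. Hence separate, penalised models.

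**The case against.** The strongest reply is that the larger losses come from chosen scenarios. The protocol gives no NSAID prevalence, no NSAID effect on D0 pain and no link with response, and both effects must act in the masking direction. A shift of 1 to 1.5 SD is a lot to assume, since section 2 counts inadequate effect or poor tolerance of analgesics or anti-inflammatories among the usual reasons for the injection. No specific masking mechanism has been put forward for symptom duration or mouth opening. All of this stands, so the loss must be stated as conditional.

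Three stronger readings are tempting, and the document does not support them.

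- A reader might infer that the plan will declare a dropped factor not predictive. Section 8-2 has no rule for reading a non-significant factor, and 8-3 promises only hypotheses.
- A reader might blame the screen for the low power. Without confounding, a true OR of 2 per SD fails the screen in about 43% of simulated trials, yet detection falls by only 0.3 points. The failure rate and the wide interval come from 40 patients.
- A reader might take the simulated percentages as properties of this plan. Section 8-2 names ANCOVA and a mixed model; Firth regression is a substitute, so the figures show what the order of steps does, not the plan's exact operating characteristics.

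It can also be said that tables of estimates belong in an analysis plan that is not shown, and that 8-2 promises to study the correlation of response with all four factors without a P threshold. That covers crude results. It does not undo the entry rule for the adjusted model, which 8-2 itself fixes.

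**Conclusion.** The point holds as a conditional weakness. Section 8-2 chooses factors for adjustment by a test that ignores the confounders it lists, so a masked pre-named factor can be dropped without an adjusted estimate. At n = 40 the screen costs about 6 to 10 points of detection under the assumed strong NSAID masking and about 1 to 2 under moderate masking. It costs essentially nothing with no confounding or with confounding in the other direction. Harsher assumptions give larger losses (Step 3), but the document supplies no figure that would select among these cases. In none of the cases examined did the screen improve detection of a real factor; what it buys is about 1 point of per-test false-positive rate. Priority is optional to moderate: the study is exploratory, but finding factors is its only aim and the change is cheap.

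**What to change.** In section 8-2:

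- Do not apply the P<0.1 screen to the four pre-named factors: D0 pain, symptom duration, limited mouth opening, and radiological lesions. Include the last only if it varies among the patients, since inclusion already requires radiographic confirmation.
- For each of the three response definitions, fit each named factor in its own binary-response model (penalised logistic, for example Firth) with the fixed set already listed: age, gender, NSAIDs and tray. Do not put all eight terms in one model.
- Report the crude and the adjusted odds ratio with 95% CI for every named factor, whatever its P value.
- Describe P of 0.05 or more as inconclusive, noting that 40 files leave an OR of about 2 per SD undecided (95% CI about 0.9 to 4.6).

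The cost is a change of wording and at most 4 x 3 = 12 adjusted models per analysis population, with no new data or patients. The downside is the rise of about 1 point in the per-test false-positive rate (about 1.4% to 2.5% in simulation).
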